### 3.10 Interventions

#### *3.10.1 Treatment*

Patients will be randomized at a 1: 1: 1 ratio to receive halofuginone 0.5mg orally once daily, halofuginone 1mg orally once daily or placebo. There will be two preparations of the halofuginone solution for the study, one in the concentration of 0.5 mg / 5 mL and the other in the concentration of 1 mg / 5 mL, as well as a solution containing placebo, which will ensure that the same volume of solution is administered for patients in both arms (0.5 mg and 1 mg) of the intervention and placebo, which will make it impossible to identify the randomized group. Thus, regardless of the group, each patient will use 5 mL of the designated solution per day, for 10 days. In case of need for hospitalization, the patient will stop using the study medication.

The study medication (intervention and placebo) will be sent to the participating center in properly identified bottles. Once the patient is randomized, a person from the clinical trial team will be responsible for delivering the medication to the patient, as well as to provide guidelines for use.

#### *3.10.2 Additional study interventions*

Knowing that the most commonly reported adverse events with the use of halofuginone in phase I trials were nausea and vomiting after taking the medication, patients who present such symptoms will be advised to prophylactic use of an antiemetic (ondansetron 4mg orally) between 30 minutes and 1h taking the study medication. This use should be maintained as long as the patient is using the study medication. If the patient does not experience nausea or vomiting with the use of the study medication, he should not use the antiemetic. Ondansetron will be provided by the study free of charge to patients who are not allergic to it. In case of allergy to ondansetron, metoclopramide 10mg will be offered as an antiemetic alternative.

In addition, there will be no other mandatory intervention in the clinical study. Patients will receive standard treatment indicated by the care team, as well as specific

guidelines on the disease. Specific treatment for COVID-19 may include, but is not limited to:

- Antibiotic therapy for secondary infection;
- Medications to treat symptoms such as fever, pain and nausea;
- Antivirals if indicated by the patient's medical team;
- Other interventions, if indicated by the patient's medical team.

### *3.10.3 Treatment interruption*

Treatment should be stopped in the following situations:

- Patient presents hospitalization; **OR**
- Patient who had validated antigen test result and later presented a negative RT-PCR result performed on first day of the participation; **OR**
- Patient who has clinical indication for use of full-dose anticoagulants; **OR**
- Presence of serious adverse events.

In the situation of treatment interruption due to negative RT-PCR test for SARS-CoV-2, no additional clinical and laboratory data will be collected.

In other situations, the patient will be instructed to stop using the study medication and there will be no additional collection of laboratory tests. Clinical data collection via online questionnaire and clinical follow-up via phone call will be maintained.

### *3.10.4 Halofuginone and dosage justification*

Halofuginone [7-bromo-6-chloro-3- [3- (3-hydroxy-2-piperidinyl) -2-oxopropyl] -4 (3H) -quinazolinone] is an analogue of the febrifugin used and approved by the FDA and the Brazilian Ministry of Agriculture, Livestock and Supply for the prevention of

coccidiosis in birds and against protozoa in cattle. The molecule has a piperidine ring that is essential for its activity.

The selected doses of halofuginone for the present study were based on safety, tolerability, pharmacokinetic and pharmacodynamic data published by de Jonge et al, which included 24 patients with a median age of 58 years (62.5% men) and with refractory solid neoplasia standard treatment.

In preclinical studies, oral halofuginone doses of 0.35mg/kg/day and 0.142mg/kg/day, which correspond to doses of 24.5mg/day and 9.94mg/day for a 70kg adult, were well tolerated for periods of 4 to 26 weeks. In rats, mortality was observed at doses of 6mg/kg/day (corresponding to 420mg to 70/kg) after 5 days of treatment. The bioavailability of oral halofuginone in rats is 51% and in pigs 72%. In animals, about 60% of the oral dose is eliminated unchanged in the faeces. The plasma half-life varies between 5 and 17 hours. In the dose escalation study in adult males, no serious adverse events were reported at doses of 0.5 mg. In 1.5mg, 2mg and 2.5mg dose increments, mild to moderate nausea and vomiting were reported, however these episodes were short-lived and resolved spontaneously.

In adults, doses of 1mg/day per day for two weeks, no dose limiting toxicity (DLT) was noted. At doses of 2mg/day, some patients experienced nausea and vomiting grade 2 with improvement after the use of prophylactic antiemetics. However, with doses of 3.5mg per day, two patients had DLT, despite the use of prophylactic antiemetics, defining that the maximum tolerated dose (MTD) was exceeded.

Halofuginone caused predominantly symptoms of gastrointestinal toxicity, manifested by nausea and vomiting that were chronologically related to the use of medication. Most patients experienced symptoms within 30 minutes to an hour after taking the medication. Fatigue was the second most common side effect. Hematological toxicity was not observed. Table 1 describes the toxicity events during the two-week treatment period:

**Table 1.** Toxicity in the first two-week cycle according to the common terminology of adverse events of the National Cancer Institute version 2.018 a

| Dose
mg/day | No. of
patients | Leukopenia |   |   |   | Neutropenia |   |   |   | Thrombocytopenia |   |   |   | Nausea |   |   |   | Vomiting |   |   |   | Fatigue |   |   |   | DLT |
|----------------|--------------------|------------|---|---|---|-------------|---|---|---|------------------|---|---|---|--------|---|---|---|----------|---|---|---|---------|---|---|---|-----|
|                |                    | 1          | 2 | 3 | 4 | 1           | 2 | 3 | 4 | 1                | 2 | 3 | 4 | 1      | 2 | 3 | 4 | 1        | 2 | 3 | 4 | 1       | 2 | 3 | 4 |     |
| 1              | 4                  |            |   |   |   |             |   |   |   | 1                |   |   |   | 3      |   |   |   | 2        |   |   |   | 3       |   |   |   | 1*  |
| 2              | 6                  |            |   |   |   |             |   |   |   |                  |   |   |   | 1      | 4 |   |   | 2        | 3 |   |   | 2       | 3 |   |   |     |
| 3.5            | 3                  |            |   |   |   |             |   |   |   |                  |   |   |   |        | 1 | 1 |   | 1        | 1 |   |   |         |   | 2 |   | 2   |
| 0.5            | 5                  | 1          |   |   |   |             |   |   |   |                  |   |   |   | 1      |   |   |   | 2        |   |   |   | 1       |   |   |   |     |
| 0.5 2x         | 7                  |            |   |   |   |             |   |   |   |                  |   |   |   | 2      |   |   |   | 1        | 1 |   |   | 3       |   |   |   | 2*  |

a Adapted from de Jong et al.  
b Abbreviations: DLT, dose-limiting toxicity.  
\* DLT for chronic administration

Seven of the 24 patients in the study experienced bleeding during treatment with halofuginone. In preclinical studies, halofuginone inhibited the migration of endothelial cells and prevented their organization in networks similar to capillary anastomoses. *In vivo* studies, no thromboembolic events or bleeding were observed. Table 2 describes the bleeding episodes and doses for each patient.

**Table 2.** Bleeding episodes a

| Patient | Cycle b | Dose         | Description                                                                                                    |

the last 3 weeks, current use of full-dose anticoagulants [warfarin, enoxaparin or new anticoagulants] or dual antiplatelet and platelet therapy to [ $<100,000/\text{mL}$ ] or ISR [international standardized ratio] $> 1.3$ ). It is reinforced that in patients who presented hemorrhagic phenomena, laboratory tests that evaluate coagulation (platelet count and levels of coagulation factors) were not altered, which reinforces the hypothesis that these hemorrhagic phenomena are primarily related to the presence of metastases in these patients.

Absorption of halofuginone after an oral dose was associated with a maximum peak of the drug at  $3.4 \pm 4.8$  hours. About 4-12% of the halofuginone administered was excreted in the urine, mainly in the first 24 hours after administration. Table 3 contains data on the pharmacokinetics of halofuginone in the study doses.

**Table 3.** Pharmacokinetics of halofuginone during the first cycle a

| Dose (mg/day) | C max (ng/mL) | T max (h) | T 1/2 (h) |
|---------------|--------------------------|----------------------|----------------------|
| 0.5           | 0.54                     | 2.8                  | 17.2                 |
| 1             | 0.88                     | 2.0                  | 31.5                 |

a Adapted from de Jong et al.  
Abbreviations: Cmax, plasma peak; Tmax, time to maximum concentration; T1/2, terminal disposal half life

Therefore, in view of the most common adverse events with the use of halofuginone (gastrointestinal symptoms such as nausea and vomiting, which were dependent on the dose administered, as well as duration of cycles), risk of bleeding, as well as pharmacokinetic properties of the drug, if by using doses of 1mg/day and 0.5mg/day in the intervention arms, excluding patients at high risk of bleeding, as well as patients who have less drug elimination.

### 3.10.5 Coding of study medication

Solutions with two different concentrations of halofuginone (0,5mg/5mL e 1 mg/5 mL) and a placebo solution will be used.

Each individual treatment solution will be identified by one of three random letters (from A to I) unique to each group. The code list will be sequential and unknown to researchers and patients, which the codes will be known exclusively by the pharmacist responsible for the study.

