### 3.9 Allocation concealment and randomization

Patients will be randomized in the proportion of 1:1:1, for the control arms, halofuginone 1mg and halofuginone 0.5mg. The randomization list will be generated electronically by an independent statistician using a specific software. Randomization will be performed in blocks and will be stratified by age (<60 years and ≥ 60 years).

The allocation concealment of the randomization list will be maintained through an automated and centralized randomization system accessed via the internet, available 24 hours a day. Patients who do not meet the eligibility criteria to participate in the study should not be recruited and randomized, and this will be considered a violation of the protocol. Patients, principal investigators and local staff will be kept blind to the allocation; only the sponsor will be aware of the blinding codes. The assessors and statisticians responsible for the results will be kept blind in relation to the allocated treatments.

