### *3.10.6 Emergency break of the designated treatment code*

Emergency breaks in the code should be undertaken only when it is necessary to treat the participant safely. Very often, discontinuation of study treatment and knowledge of the possible designations of this treatment are sufficient to treat a participant who has an emergency condition.

Emergency breaks in the treatment code will be carried out using the study exclusive email and phone for this purpose.

When the investigator contacts the coordinating center to break a treatment code for a patient, he must provide the requested patient identification information and confirm the need to break the code for that patient. The investigator will then receive details of treatment with the investigational drug for the specified participant. An evaluation will be carried out by the team of the coordinating center and the designated doctor. After an emergency code break, the participant will follow the study in accordance with the protocol, but must discontinue the treatment of the study.

**Figure 1.** Emergency blinding break flowchart

[figure not shown]

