### 3.10.7 Adhesion

Adherence to the protocol will be guaranteed with the training of all investigators and study staff.

Once randomized, patients will receive guidance on the dosage of the study medication, mode of use and duration of treatment. Patients will also receive a newsletter that will contain clear guidelines on the use of the medication. During visits to collect exams on the fifth and tenth days, guidelines on dosage and use will be reinforced for the patient. On the tenth day, together with the collection of exams, the study medication bottles will be collected and sent to the pharmacist at the coordinating center, where the quantity of remaining medication will be measured, thus allowing inferences about the patients' adherence to treatment.

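### Medication letters are tied to arms, so an emergency code break also reveals other patients on the same letter at that site; the sections on who holds the codes need reconciling

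*Protocol*

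**What the plan says.** Labelling. Protocol section 3.10.5 describes two halofuginone concentrations and a placebo, coded as follows: "Each individual treatment solution will be identified by one of three random letters (from A to I) unique to each group". It calls the code list sequential, without explaining the term, and mentions no patient or kit number.

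Handling. Under section 3.10.1 the medication "will be sent to the participating center in properly identified bottles", and after randomization "a person from the clinical trial team will be responsible for delivering the medication to the patient".

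Code break. Section 3.10.6 routes the request through the coordinating center ("When the investigator contacts the coordinating center to break a treatment code for a patient") and then states: "The investigator will then receive details of treatment with the investigational drug for the specified participant".

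Custody. Section 3.9 says that "only the sponsor will be aware of the blinding codes" and, in its next sentence, requires outcome assessors and statisticians to stay blind. Section 3.10.5 says that "the codes will be known exclusively by the pharmacist responsible for the study". Section 3.10.7 places a pharmacist at the coordinating center: returned bottles are "sent to the pharmacist at the coordinating center". Section 13.1 treats the coordinating center and the sponsor as one body.

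**The concern.** A code break should disclose one patient. If the label identifies an arm rather than a patient, the disclosed treatment also gives the meaning of the label. The investigator can apply that meaning to every other patient whose letter is known at the site, including patients still under follow-up and any enrolled later on that letter. Nothing in the protocol prevents this. The equal 5 mL volumes in section 3.10.1 hide the concentration but not the meaning of a decoded letter.

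Several outcomes rest on the judgement of patients or site staff who are meant to be blind:
- time to symptom resolution, from the daily online questionnaire;
- the two non-hospitalized levels of the Day 14 scale, collected by telephone by the site team;
- adverse events and their causality;
- drug-related discontinuation.

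The custody wording raises a second question. If the whole sponsor holds the codes, they sit in the same organization that receives all adverse events (section 8.6.2), controls data quality and performs the statistical analysis (section 11.1).

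**Working it through.** The plan states no figure on this point, so there is nothing to reproduce. The check is a count, followed by a comparison of sections.

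**Inputs**
- Letters A to I: 9 (section 3.10.5)
- Arms: 3, allocated 1:1:1 (section 3.9)
- Patients: 150, i.e. 50 per arm (section 5); 3 × 50 = 150 agrees
- Sites: 2 to 5 (section 3.2)
- Assumed, because the protocol does not say: equal site sizes and equal use of the nine letters

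**Letters per arm:** 9 / 3 = 3.

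**Other patients on the same letter at the same site:** (150 / sites) / 9 − 1.
- 2 sites: 75 / 9 − 1 = 7.3
- 3 sites: 50 / 9 − 1 = 4.6
- 4 sites: 37.5 / 9 − 1 = 3.2
- 5 sites: 30 / 9 − 1 = 2.3

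**Upper bound, if letters are shared and known across sites:** 150 / 9 − 1 = 15.7 others.

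**Partial information on the other letters.** If it is known that each arm has three letters, then after one break each of the remaining 8 letters has probability 2/8 of belonging to the revealed arm and 3/8 for each other arm, instead of 1/3 each.

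**Alternative reading of the sentence: three letters in all, one per arm.** Others at the same site would be 75 / 3 − 1 = 24 with 2 sites and 30 / 3 − 1 = 9 with 5 sites. Trial-wide the figure is 50 − 1 = 49. The nine-letter reading is therefore the milder one.

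**With a patient-level code:** 0 others under any of these assumptions.

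**Custody, side by side**
- Section 3.9: the sponsor alone knows the codes; assessors and statisticians stay blind.
- Section 3.10.5: the study pharmacist alone knows them; the list is unknown to researchers.
- Section 3.10.6: the investigator calls the coordinating center and then receives the treatment. The coordinating center team and a designated doctor carry out an evaluation. The text does not name who reads the code.

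The pharmacist's place at the coordinating/sponsoring center narrows the gap, since the two holders can be read as an organization and a person within it. The scopes still differ: one pharmacist is not the whole sponsor.

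**The case against.** The strongest reply is that the scheme is safer than it looks.

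- **Code breaks are restricted.** Section 3.10.6 allows them only where needed to treat the participant safely, and notes that stopping the study drug is often enough. The disclosure is formally limited to one participant. This stands as to frequency, but it does not alter what a break reveals.
- **The wording is ambiguous.** The text does not say outright that the letter is printed on the bottle or is the only mark there, and kit numbering may be set in a pharmacy manual. This stands as a limit. Even so, solutions identified by letter and sent out in identified bottles point to a visible letter. Several letters per arm are also a partial safeguard, already credited in the 2 to 7.
- **Custody can mostly be reconciled.** The pharmacist sits within the sponsor, and section 3.9 already requires blind assessors and statisticians. The flowchart in section 3.10.6 (Figure 1) is not shown and may name who releases a code. What remains is mainly a matter of wording, but it needs settling.

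A reader might also draw stronger conclusions, which the documents do not support:

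- **One break unblinds about a ninth of the trial, or three breaks a third.** This needs letters shared across sites and an investigator who knows other sites' letters, and the protocol states neither. The three-break case also needs three different letters, pooled knowledge and a break rate that the protocol does not give.
- **Concealment of later allocations is broken.** Randomization is central and web-based, stratified by age only, with unstated block sizes (section 3.9). Knowing what one letter means does not show which letter the system will issue next.
- **Staff can decode letters from nausea and vomiting alone.** With about 3 to 8 patients per letter per site such a comparison says little, and section 3.8.4 lists both among the symptoms collected for the disease itself.

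**Conclusion.** The point holds in a limited form. As written, the labels identify arms, and a code break reveals about 2 to 7 other patients at the same site. This assumes nine letters in equal use, 2 to 5 equal sites, and a letter that site staff can see. The trial-wide figure of about 16 others is an upper bound that depends on letters being shared and known across sites.

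The primary outcome is a viral load measured in a central laboratory (section 3.11.4) and is largely protected. Hospital admission and mechanical ventilation are also fairly objective. The exposure lies in the softer secondary and safety outcomes. No sample-size, power or significance figure is affected. This is a worthwhile, cheap improvement and does not threaten the main result.

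The custody statements in sections 3.9 and 3.10.5 differ as written and should be reconciled with section 3.10.6. They do not show that the analysts will be unblinded, because section 3.9 requires the opposite.

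**What to change.** 1. In section 3.10.5, replace the group letters with a unique bottle or kit number per patient, drawn from a scrambled list and issued by the central web randomization system already described in section 3.9. A code break then reveals one patient.
2. Make sections 3.9, 3.10.5 and 3.10.6 agree on who holds the codes and who releases one. One option is a named unblinded pharmacist at the coordinating center, separate from the staff who handle data, adverse events and analysis. This would fit the existing requirement that assessors and statisticians stay blind.

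The cost is relabelling, a number table in the existing system, and slightly more complex site stock, because each site needs a small buffer for each arm. Item 2 is a change of wording and a named role. Neither item alters any dose, treatment rule or analysis.

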### *3.10.6 Emergency break of the designated treatment code*

Emergency breaks in the code should be undertaken only when it is necessary to treat the participant safely. Very often, discontinuation of study treatment and knowledge of the possible designations of this treatment are sufficient to treat a participant who has an emergency condition.

Emergency breaks in the treatment code will be carried out using the study exclusive email and phone for this purpose.

When the investigator contacts the coordinating center to break a treatment code for a patient, he must provide the requested patient identification information and confirm the need to break the code for that patient. The investigator will then receive details of treatment with the investigational drug for the specified participant. An evaluation will be carried out by the team of the coordinating center and the designated doctor. After an emergency code break, the participant will follow the study in accordance with the protocol, but must discontinue the treatment of the study.

**Figure 1.** Emergency blinding break flowchart

[figure not shown]

### 3.10.7 Adhesion

Adherence to the protocol will be guaranteed with the training of all investigators and study staff.

Once randomized, patients will receive guidance on the dosage of the study medication, mode of use and duration of treatment. Patients will also receive a newsletter that will contain clear guidelines on the use of the medication. During visits to collect exams on the fifth and tenth days, guidelines on dosage and use will be reinforced for the patient. On the tenth day, together with the collection of exams, the study medication bottles will be collected and sent to the pharmacist at the coordinating center, where the quantity of remaining medication will be measured, thus allowing inferences about the patients' adherence to treatment.

### *3.10.8 COVID-19 negative confirmatory exam*

Patients who are included in the study based on the results of rapid tests such as GeneXpert Cepheid® (ANVISA Registration Number 81062710039) or commercially analogous, or rapid Antigen test (COVID - 19 Ag ECO Test - ANVISA Registration Number 80954880133) who have a negative laboratory diagnosis by RT-PCR for SARS-CoV-2 will be contacted via telephone where they will be informed to cease the use of the study medication. A study technician will go to the participant's residence to remove the study medication. The participant will be asked to allow the use of the data collected so far for the safety analysis of halofuginone, for analysis by intention to treat and other analyses.

